## Methods

### Study design and setting

A two-arm randomized controlled trial (RCT) of the efficacy of an Internet-based stress recovery intervention for adolescents is planned. Participants will be adolescents aged 15–19 years, studying in high school and who have indicated exposure to daily life stressors, such as school or interpersonal stressors. In order to achieve the objectives of the study, the planned sample size is 300 adolescents from Lithuania. To assess the efficacy of the 6-module four-week psychosocial intervention, the evaluation in the intervention and care as usual (CAU) groups will be carried out at the three-time points: (1) pre-intervention, (2) post-intervention, and (3) at the 3-month follow-up. These measurements will assess adolescents’ stress recovery experiences, adjustment, perceived stress, depression, anxiety, psychological well-being, and positive social support. The demographic data questionnaire will be presented at the pre-intervention test, while questions on the evaluation of the program will be asked in the follow-up. Implementing the intervention will not require alteration to usual care pathways (including the use of any medication), and these will continue for both trial arms. There are no restrictions regarding concomitant care during the trial. Both study groups will be provided with the information about psychological support options at their school. All participants of this study will have the same access to mental health care as all adolescents in Lithuania. Details of study enrolment, intervention, and assessments are presented in Table 1.

**Table 1 Tab1:** Enrollment, interventions, and assessments of the FOREST-A

	Enrollment	Allocation	Post-allocation	
Time point	*t*_*1*_		*t*_*2*_	*t*_*3*_
Enrollment				
Informed consent	X			
Informed parent consent	X			
Assessment	X			
Eligibility screen		X		
Randomization		X		
Final allocation		X		
Access to intervention				
Intervention group		X		
Care as usual group				X
Assessments				
Recovery experiences	X		X	X
Adjustment	X		X	X
Stress	X		X	X
Depression	X		X	X
Anxiety	X		X	X
Psychological well-being	X		X	X
Perceived positive social support	X		X	X

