### Randomization

Participants will be randomly allocated to either the intervention group or the care as usual group (1:1 allocation ratio). Randomization will be carried out by an independent researcher using the random number calculation procedure at www.random.org. Adolescents in the intervention group will receive access to the FOREST-A intervention immediately after allocation, while those in the care as usual group condition will have the possibility to access social or mental health services in the community.

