### Intervention condition

FOREST-A is an online psychosocial intervention program for adolescents aimed at enhancing stress recovery skills. FOREST-A was adapted from the stress recovery program developed specifically for healthcare staff (details of the program and description of content can be found in the study protocol by Jovarauskaite et al., 2021). The program was found to be effective in improving stress recovery skills of psychological detachment (*d* = 0.83), relaxation (*d* = 0.93), mastery (*d* = 0.64), and control (*d* = 0.46) at post-treatment, and all, except control, were improved at the 3-month follow-up. Users also reported positive feedback on good usability of the intervention [15]. The program is based on cognitive behavior therapy (CBT), including the third-wave CBT [17] mindfulness—approach. It is an online intervention that can be used via a computer, tablet, or smartphone. The program is comprised of six main modules:Introduction. The first session provides information about the program and its usage, psychoeducation and exercises related to stress, burnout, and four recovery skills (relaxation, psychological detachment, mastery, and control).Relaxation. In order to enhance participants’ relaxation skills, the second session provides psychoeducation and exercises related to physical sensations, body relaxation, and sleep.Psychological detachment. The third session provides opportunity to enhance participants’ psychological detachment skills. It includes psychoeducation and exercises related to psychological detachment (both physical and mental) and intrusive thoughts.Mastery. The fourth session provides psychoeducation and exercises related to mastery of daily life (other than school-related) as well as physical activity. These activities include enjoyable tasks that require some competence (e.g., reading, cooking, and doing sports, among others). The participant chooses what is relevant for him/her and what can bring the feeling of being competent. Its main aim is to enhance participants’ mastery skills in individually chosen activity or activities.Control. The fifth session provides psychoeducation and exercises related to control over one’s life and the day’s structure. By reflecting on daily goals and changing unnecessary and bothering activities to more pleasant and relaxing ones, the participant is encouraged to take responsibility for his/her well-being. Its main aim is to enhance participants’ control skills.Summary and keeping the change alive. The last session summarizes the program with its main aspects, psychoeducation, and exercises related to consolidation of new skills. Its main aim is to enhance the integration of new skills into participants’ lives.

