### Primary outcome

The Recovery Experience Questionnaire (REQ) [18] will be used to measure stress recovery. The REQ was previously translated into Lithuanian and used in the adult sample in Lithuania [15]. The revised child and adolescent version of the REQ adapted for children and adolescents (REQ-CA) will be used in this study. The REQ-CA comprises 16 items and four subscales (with four items per each subscale) to measure recovery experience components: psychological detachment, mastery, relaxation, and control. Participants are asked to provide responses to each of the items on a 5-point Likert scale, ranging from *Totally disagree* (= 1) to *Totally agree* (= 5). The total score of the REQ-CA is a sum of all scale items and ranges from 16 to 80. The REQ-CA subscales scoring is a sum of items comprising the subscale with a range from 4 to 20. Higher scores on the REQ-CA and subscales indicate higher stress recovery skills. Previous studies showed good psychometric properties of the REQ in adult samples [15, 19].

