### Statistical analyses

Repeated measures ANOVA will be applied to evaluate group × time effects of the intervention. Within-group and between-group effect sizes will be used to estimate the role of intervention on the change of the primary and secondary outcomes.

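### The stated efficacy test is a 2-df group × time interaction that is valid but names no time or direction, and it uses the pre-allocation score as an outcome level, not as a covariate

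*Protocol article*

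**What the plan says.** Under Statistical analyses, the protocol article plans a repeated measures ANOVA to "evaluate group × time effects of the intervention". It adds: "Within-group and between-group effect sizes will be used to estimate the role of intervention on the change of the primary and secondary outcomes". No time point, planned contrast or covariate is attached to either sentence.

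Study design and setting lists the assessments: "1) pre-intervention, (2) post-intervention, and (3) at the 3-month follow-up". They are called t1, t2 and t3 here, as in Table 1. That table puts the REQ-CA at all three, with t1 before randomisation. Primary outcome opens with "The Recovery Experience Questionnaire (REQ) [18] will be used to measure stress recovery" and describes the scoring, again without a time point. On size, the article says "the planned sample size is 300 adolescents from Lithuania", allocated 1:1.

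**The concern.** The main objective, at the end of Background, is efficacy judged by comparing outcomes between FOREST-A and care as usual. The omnibus interaction rejects whenever the two arms' profiles over t1, t2 and t3 are not parallel. A benefit at t2 only, a benefit at t3 only, harm at t3 only, or opposite effects at t2 and t3 can each produce it. A claim of efficacy then needs a further contrast, and the article does not say which. If that choice is made after the data are seen, the time that looks better can become the headline.

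The choice can matter. For the adult predecessor programme, Intervention condition reports four skills improved at post-treatment, but later "all, except control, were improved at the 3-month follow-up". For one of the four, the two times gave different answers.

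The second issue is efficiency. The t1 score is measured before allocation, so random assignment makes its expected mean equal in the two arms. The planned model does not use that fact.

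**Working it through.** **Inputs from the article.** Two arms, three assessments, 300 participants at 1:1, so 300/2 = 150 per arm. Interaction df = (2−1)(3−1) = 2. The article gives no power calculation, so there is no stated power figure to reproduce.

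**Assumed inputs.** Two-sided alpha 0.05, SD 1 at each time, the same correlation r between any two times (0.3, 0.5, 0.7), complete data, and between-arm effects d2 at t2 and d3 at t3. The expected t1 difference is 0.

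**What the interaction reacts to.** The noncentrality is λ = n·Σ(dₖ−d̄)² / [2(1−r)], with n = 150 per arm and df 2 and 2(300−2) = 596. At r = 0.5:

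- d2 = 0, d3 = −0.30 (harm at follow-up only): Σ = 0.06, λ = 150×0.06/1 = 9.0, power 77%.
- d2 = +0.30, d3 = 0 (benefit at post-test only): the same Σ, λ and power, 77%.
- d2 = +0.20, d3 = −0.20: Σ = 0.08, λ = 12.0, power 88%.

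The F statistic cannot tell the first two apart.

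**Change score against covariate.** The between-arm difference in change from t1 has variance 4(1−r)/n. The ANCOVA difference has variance 2(1−r²)/n. The ratio is (1+r)/2, or 0.75 at r = 0.5.

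**Like for like: two joint tests of t2 and t3.** The baseline-adjusted joint test has λ = (n/2)·d′S⁻¹d, where d = (d2, d3) and S has 1−r² on the diagonal and r−r² off it, with df 2 and 297. At r = 0.5, S⁻¹ has 1.5 on the diagonal and −0.5 off it.

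- Flat 0.30: λ = 75×0.09×2 = 13.5.
- 0.30 and 0.15, in either order: λ = 75×(0.135 − 0.045 + 0.03375) = 9.28.

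| Effects at t2, t3 (r = 0.5) | Planned interaction | Baseline-adjusted joint test | ANCOVA at t2 only |
|---|---|---|---|
| 0.30, 0.30 | 77% | 92% | 85% |
| 0.30, 0.15 | 64% | 78% | 85% |
| 0.15, 0.30 | 64% | 78% | 32% |
| 0, 0.30 | 77% | 82% | 5% |
| +0.20, −0.20 | 88% | 88% | 51% |

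The last column uses λ = n·d2²/[2(1−r²)] with df 1 and 297. For d2 = 0.30 this is 150×0.09/1.5 = 9.0. A simulation of 4,000 trials for the flat row gave 77.4% for the interaction and 85.3% for ANCOVA at t2, in agreement.

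**Sensitivity to r and d.** For flat 0.30, ANCOVA at t2 against the interaction is 78% against 61% at r = 0.3, and 95% against 94% at r = 0.7. For flat 0.46, the smallest post-treatment effect quoted for the adult programme, it is 99% against 95% at r = 0.3, and above 99% against 99% at r = 0.5.

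**The case against.** A reader might infer that the interaction does not test efficacy at all. The documents do not support that. Because allocation is random, a null interaction means no arm difference at t2 and none at t3, so the test is valid. A difference that appears only at t3 is a real difference at a planned assessment. Rejecting in both directions is also a property of any two-sided test. What remains is that the omnibus F attaches no signed estimate to a named time.

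A reader might also infer that baseline is ignored. It is not: with t1 as a level of time, the interaction compares change from baseline. What is absent is t1 as a covariate, which is a matter of precision and not of bias.

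The strongest objection concerns power. Setting a joint test against a single-time test at the assumed peak flatters the latter, and the 0.15-then-0.30 row reverses the ranking (32% against 64%). Sharing alpha between t2 and t3 (0.025 each) gives each flat-0.30 ANCOVA contrast 77%, no better than the interaction. This stands, so a general statement that power is wasted cannot be made from the article. It does not remove the like-for-like gain between the two joint tests, although that gain vanishes when the two effects cancel.

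Finally, the planned between-group effect sizes will give direction and size, and contrasts or covariates may be set out in the full protocol, which the article says is available on request. That is fair as far as missing detail goes. The point here is about the method the article does state, and those effect sizes carry no time, test or model. The within-group ones are not randomised comparisons.

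**Conclusion.** The point holds in limited form. That the stated test is tied to no named time or direction follows from the article alone and needs no assumed figure. The efficiency point is secondary and rests on assumed d, r, alpha and full retention. For d = 0.30 and r = 0.5, the baseline-adjusted joint test gains about 14 to 15 points when the effect is flat or half-size at one time, and about 5 points when it is at one time only. Against a single ANCOVA at t2 with a flat effect, the gap runs from about 16 points at r = 0.3 to 1 point at r = 0.7. If adolescents respond as strongly as the adults did, little power is at stake. The article itself warns, in the Discussion, that outcomes in adolescents might differ. This is an improvement worth making, not a flaw that invalidates the trial.

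**What to change.** Name the primary time point for REQ-CA. Make the primary estimate the between-arm difference at that time with a 95% CI, from ANCOVA on the t1 REQ-CA score or from a mixed model of t2 and t3 with t1 as covariate (or with baseline means constrained equal). Take the other time's contrast from the same model, and report the group × time interaction as supportive.

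If the sponsor has no firm view on when the effect should be largest, test t2 and t3 jointly in the baseline-adjusted model, or split alpha between them, and say so in advance.

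The cost is wording only, since Table 1 already schedules REQ-CA at t1. The trade-off is that a single primary time gives up power if the effect falls mainly at the other one, so the choice needs a stated reason before the data are seen.

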Internet-based stress recovery intervention For Recovery from Stress—Adolescent Version (FOREST-A) was created to address the need to develop and enhance stress recovery skills in adolescents exposed to life stressors and experiencing high levels of stress. The intervention aims to prevent mental health problems in stressor-exposed adolescents. The FOREST-A intervention is grounded on a mindfulness-based approach, which has been recognized as improving the self-regulation of emotions, behavior, and cognitive processes. These skills contribute to coping with stress [13]. FOREST-A was developed as a modification of the FOREST intervention, initially created as a stress recovery intervention for healthcare workers [14]. Findings from the RCT study revealed high effect sizes of the FOREST intervention [15]. The FOREST-A program and design of the study were adapted to the needs of adolescents. At the same time, the primary approach and structure of the modules remain similar to the original FOREST intervention.

The main objective of the study is to evaluate the efficacy of the Internet-based stress recovery intervention for adolescents (FOREST-A) in a two-arm RCT by comparing outcomes of the stress-related psychological indicators in the intervention and care as usual (CAU) groups. The secondary objectives of the study are to evaluate the effects of the FOREST-A: (1) on stress recovery skills, (2) on adjustment disorder symptoms, (3) on anxiety symptoms, (4) on general health and well-being, (5) on perceived social support, and (6) to evaluate the FOREST-A itself, how user-friendly and acceptable for study participants it is.

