All participants who provided informed consent will be asked to complete the measures in a secure online platform designated for the research survey. Eligibility for inclusion in the study will be assessed based on the responses from participants at the pre-intervention assessment. Those who do not meet the eligibility criteria will be informed of this and given information on other options for psychosocial services in the school or community (Fig. 1).

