### Participants and inclusion/exclusion criteria

The information about the intervention would be sent to various high school institutions across Lithuania. The invitations to participate in the study and intervention would be spread in collaboration with contact persons in schools.

The sample will comprise self-referred adolescents who experience high levels of stress in daily life. The inclusion criteria for the participation: (1) adolescents aged 15–19, (2) studying at the high school in Lithuania; (3) comprehending Lithuanian, (4) parental and own consent for minor-aged participants (< 18 years) or only own consent for adolescents aged 18 years or older to participate in the study provided, (5) have access to a device (such as a tablet, phone or computer) with an Internet connection. Exclusion criteria: (1) acute psychiatric condition/crisis, (2) no recent life-stressor exposure, or low levels of stress.

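### Within-group effect sizes are given a share in estimating the intervention's role, which a one-arm pre-post change cannot do in a sample selected for high stress at baseline

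*Protocol article*

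**What the plan says.** The protocol article's Statistical analyses section has two sentences. The first names the main analysis: "Repeated measures ANOVA will be applied to evaluate group × time effects of the intervention". The second reads: "Within-group and between-group effect sizes will be used to estimate the role of intervention on the change of the primary and secondary outcomes". It gives the within-group and between-group figures one shared purpose. Nothing elsewhere in the article ranks them or restricts the within-group figure to description.

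The main objective, at the end of the Background, is to evaluate efficacy "by comparing outcomes of the stress-related psychological indicators in the intervention and care as usual (CAU) groups", which is a comparison between arms.

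On who is enrolled, Participants and inclusion/exclusion criteria says: "The sample will comprise self-referred adolescents who experience high levels of stress in daily life". One of the exclusions is "no recent life-stressor exposure, or low levels of stress". No instrument or cut-off is given for this. Study design and setting adds: "Eligibility for inclusion in the study will be assessed based on the responses from participants at the pre-intervention assessment". The screening responses are therefore also the pre-test responses. The same section lets usual care, medication included, continue unrestricted in both arms, and gives both arms information on psychological support at school.

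**The concern.** A pre-post change in the intervention arm is the sum of several things: any effect of the programme, regression to the mean caused by selecting on the baseline measurement, natural recovery from time-bound school and interpersonal stressors, and whatever usual care contributes. Only the contrast with the care as usual arm removes the last three, because randomisation spreads them equally over both arms. A within-group effect size cannot separate them, yet the sentence uses it to estimate what the intervention did.

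What is at stake is the reported size of the effect. The sentence covers the primary outcome and all secondary outcomes, and there are two assessments after baseline. A favourable within-group figure could be presented as the intervention's contribution on an outcome where the arms do not differ.

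**Working it through.** The article states no figure on this point, so there is none to reproduce. What follows illustrates the size on assumed inputs.

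**Inputs from the article.** "the planned sample size is 300 adolescents from Lithuania", allocated 1:1, so 300 / 2 = 150 per arm. Selection is for high stress on the pre-test responses. The primary outcome is a recovery scale, REQ-CA, which is not said to be the selecting measure.

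**Assumed inputs.** The share *p* selected, the retest correlation ρ, and the correlation *r* of an outcome with the selecting score. The article gives none of them. Normal scores and zero programme effect are also assumed.

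**Step 1: the selecting score itself.** If the top share *p* is kept, the mean of those selected lies λ = φ(c)/p above the population mean, in population SDs, where c is the cut-off. The expected change at retest is (1 − ρ) × λ.

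| p | λ = φ(c)/p | ρ = 0.7 | ρ = 0.5 |
|---|---|---|---|
| 0.76 | 0.311 / 0.76 = 0.409 | 0.3 × 0.409 = 0.12 | 0.5 × 0.409 = 0.20 |
| 0.50 | 0.399 / 0.50 = 0.798 | 0.3 × 0.798 = 0.24 | 0.5 × 0.798 = 0.40 |
| 0.30 | 0.348 / 0.30 = 1.159 | 0.3 × 1.159 = 0.35 | 0.5 × 1.159 = 0.58 |

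The range is 0.12–0.58 SD. The share of 0.76 is only a lenient assumption. The 76% in the Background is the prevalence of stressor exposure over a year, not a share above a cut-off on a score.

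**Step 2: an outcome only correlated with the selecting score.** The expected change is r × (1 − ρ) × λ. Here p runs from 0.25 to 0.75, ρ from 0.5 to 0.8 and r from 0.2 to 0.5.

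- Smallest: p = 0.75, λ = 0.424, so 0.2 × 0.2 × 0.424 = 0.017, about 0.02 SD.
- Largest: p = 0.25, λ = 1.271, so 0.5 × 0.5 × 1.271 = 0.318, about 0.32 SD.

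**Step 3: within-arm against between-arm with no programme effect.** A simulation of 2,000 trials used about 300 participants per trial, the top half selected, ρ = 0.6 and no dropout. Effect sizes are in units of the selected sample's baseline SD, which is smaller than the population SD, so the figure for the selecting score is larger than step 1 would give (0.4 × 0.798 = 0.32 population SD).

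| Outcome | Within-arm d | Within-arm test p < 0.05 | Between-arm d | Between-arm test p < 0.05 |
|---|---|---|---|---|
| Selecting score | 0.53 | 99.6% | 0.00 | 5.3% |
| r = 0.5 with it | 0.17 | 59% | 0.00 | 5.0% |
| r = 0.3 with it | 0.10 | 25% | 0.00 | 4.9% |

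The within-arm tests are shown only to set the bias against sampling error; the article plans no such tests. The between-arm contrast of change stays at zero with the nominal error rate in all three cases. Natural recovery and usual care are not in these figures and would add to the within-arm change.

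**The case against.** The strongest reply is that the efficacy analysis is already the right one. The group × time test comes first, the stated objective is between arms, and between-group effect sizes stand in the same sentence as the within-group ones. A reader of the results would see a null interaction and a null between-group effect size beside any within-group figure. This stands: the planned test is not biased by the mechanism described here, and the fault is confined to one sentence.

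The selecting measure and cut-off are also unknown. Selection could rest partly on the yes/no stressor list, and a lenient cut-off would produce little regression. This stands too, which is why the size is given only as a range on assumptions.

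The article is also a condensed account, and its Data Availability section says the full protocol can be requested. Which effect size is primary could be settled there. This does not answer the point, because the point rests on what the article states. The sentence positively assigns within-group figures the job of estimating the intervention's role.

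Last, baseline adjustment and a confidence interval go further than the defect requires. That is correct in part: the simulation used unadjusted change scores and the bias was already gone. What removes the bias is relying on the between-arm difference alone.

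**Conclusion.** The point holds as a fault in the effect-size sentence. As worded, a one-arm pre-post effect size is used to estimate the intervention's role in a sample selected for high stress on its own baseline, with usual care running in both arms. It cannot do that, and it does not match the between-arm objective. On assumed inputs the spurious part is about 0.12–0.58 SD on the selecting score and roughly 0.02–0.32 SD on an outcome only correlated with it. The true size cannot be derived from the documents.

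Three stronger readings are not supported:

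- A reader might infer that the trial's efficacy test is biased. It is not; the group × time contrast is randomised.
- A reader might infer that the plan is to set significance in one arm against non-significance in the other. Nothing in the article proposes that.
- A reader might apply the 0.12–0.58 SD range to REQ-CA, or take some regression as certain on every scale. That range concerns only a selecting score that the article does not identify. On REQ-CA the regression is expected to be smaller, in proportion to its correlation with that score.

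Reporting within-group change is not itself objectionable. Using it to estimate the effect of the intervention is.

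**What to change.** Reword the second sentence of Statistical analyses to say that the effect of the intervention on the primary and secondary outcomes is estimated only by the between-arm difference, adjusted for baseline and given with a 95% confidence interval. Add that within-group changes are reported descriptively, for both arms side by side, with no efficacy statement drawn from them.

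This needs no new data and no change of design. The cost is one sentence, and a reported effect that may look smaller than the within-group figure would have done.
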